### 2.10. Part II: Experimental CPTs

During the break between calibration and the second CPT, the subject will receive the information related to the group they are randomized into. For the deceptive placebo group, the video will describe the history of hygiene and correct method for washing hands. For the educated placebo group, the video will be an educational video about placebo, its physiology, and the use of OLP. Movies are similar in terms of duration (~11 min), image quality, and format. After both videos, there will be a time where questions can be answered by the investigators. The educated placebo group will fill out a questionnaire regarding their knowledge of the placebo effect before watching the educational video.

The test phase will be divided into two parts in a random sequence to compensate for habituation effect: deceptive placebo CPT (CPTp) or educated placebo (CPTe) and control CPT (CPTc). For the CPTp and CPTe, two milliliters of the neutral placebo cream are applied beforehand following a standardized procedure: four round-trips on the forearm along its submerged part and on the dorsal and palmar side of the hand and an expectancy questionnaire is filled out. The immersion time (t) in cold water will be that previously calibrated.

While applying the neutral cream, the examiner will explain to the deceptive placebo group, that “it is a cream effective in fighting cold-related pain.” In the Educated placebo condition, the examiner states that it is “a placebo cream, containing no active substance that is effective in fighting cold-related pain. All the mechanisms shown in the previous film will be at work. In a way, your brain will be secreting the active components itself.”

Under the control condition, no cream will be applied.

The examiner will be aware that the same placebo cream is used for the two groups, in order to simulate real situations in which the practitioner administering or prescribing the placebo does so with full knowledge of its presence. The patient will not be blinded in the OLP group and will be blinded in the deceptive placebo group. The analyst will be blinded to group allocation.

### 2.11. Part III: Subject Debriefing

After all three CPTs, all subjects are asked to fill out the questionnaire on their knowledge of the placebo effect. One group (deceptive placebo group) is naive to this questionnaire and the other is filling it out again after having viewed an educational video approximately 40 min ago. This will allow for controlling information retention. Subjects then fill out a questionnaire on their perception of the research hypothesis as well as their perception of the investigators.

After the inclusion is finished, a debriefing session is conducted by the main investigator in order to explain the research protocol and the deception if one has taken place. This is done in order to be sure patients understand what the research was about and to answer any questions left by the protocol. This debriefing also allows to be sure the pain stimulation was well lived through.

Figure 2 is a detailed flow chart of the research protocol. From top to bottom are the three phases of the protocol. The white boxes are the procedures common to both groups.

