### 2.3. Assessment

The primary end point will be the difference in pain intensity, assessed on a 100-point visual analogue scale (VAS), between the educated OLP and the deceptive placebo treatments at the end of the placebo condition CPT. We have chosen pain intensity as opposed to pain threshold because it involves less motivational and cognitive components [33].

The main secondary end point will be, for each subject, the difference in pain intensity, also assessed by VAS, between open or deceptive placebo versus no-treatment control. Secondarily, a questionnaire (inspired by Hughes et al.’s data [34]) measuring knowledge regarding the placebo effect will be completed by all the subjects after the study and also before the educational video for the educated placebo group. In addition, all the subjects will complete another questionnaire about their perception of the investigators and of the study [35]. Blood pressure (BP) and heart rate (HR) values will be obtained before, during, and after each CPT by means of an automatic blood pressure monitor. Finally, subject’s anxiety will be evaluated through heart rate variability. Before the CPT treatment, an expectancy questionnaire will be used [36].

We expect to find a non-inferiority between both groups on the main end point. Considering the nature of the dependent variables and the choice of the painful stimulation, we expect a high interindividual variability. This has been limited as best as possible by the cross-over conducted in both arms of the study.

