### 2.4. Subjects

Participants are to be recruited via advertisements for a study of a painkiller cream, on the Grenoble University campus. Inclusion criteria are: being aged between 18 and 40 years old, registered to the national healthcare, having understood and signed the written consent. Non-inclusion criteria were the following: legal impossibility to participate to the protocol (i.e., pregnant women, people deprived of their liberty) or affections modifying the painful stimulus used (any known pathology affecting the venous, arterial, or lymphatic system, diabetes, cardiac affections, asthma, frostbite on the hand, epilepsy, hand arthritis, lupus erythematosus, and allergic reactions to the cream, under pain regulation medication).

All medication that could impact pain sensation, such as painkillers or psychotropics, have to be stopped three weeks prior to experiment, as will alcohol in the 24 h prior to the experiment.

Socio-demographic information will be collected in order to control the impact of these variables in the representation of the placebo effect and consequently expectations towards the treatments.

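### In the deceptive arm, the placebo-knowledge questionnaire comes just before the question on the perceived research hypothesis, so those answers may reflect the preceding form

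*Protocol article*

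**What the plan says.** Section 2.11 sets out the end of the session in sequence.

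- First comes the knowledge form: "After all three CPTs, all subjects are asked to fill out the questionnaire on their knowledge of the placebo effect". On prior exposure it adds: "One group (deceptive placebo group) is naive to this questionnaire".
- Next comes the perception form: "Subjects then fill out a questionnaire on their perception of the research hypothesis as well as their perception of the investigators".
- Disclosure comes last: "After the inclusion is finished, a debriefing session is conducted by the main investigator in order to explain the research protocol and the deception".

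Section 2.3 lists the perception form among the secondary measures, without giving its position: "all the subjects will complete another questionnaire about their perception of the investigators and of the study".

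Up to that point the deceptive arm has been given the following:

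- Recruitment (section 2.4): "Participants are to be recruited via advertisements for a study of a painkiller cream".
- Video (section 2.10): "For the deceptive placebo group, the video will describe the history of hygiene and correct method for washing hands".
- Statement when the cream is applied (section 2.10): "it is a cream effective in fighting cold-related pain".

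Sections 2.2 and 2.10 describe this arm as blinded. Section 2.13 assigns between-group differences on the remaining endpoints to Student's t-test for independent samples.

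**The concern.** A question about what the study was testing is informative only if the subject has not just been told. In the stated order, a deceptive-arm subject answers a set of items on the placebo effect and is then asked for the hypothesis. A subject who believed the message throughout the CPT can now name placebo. So can a subject who had suspected it all along, and the two answers look alike. The educated arm has known since its video and its own earlier knowledge questionnaire, so the cue is new in one arm only.

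Two uses of the form suffer. The first is the comparison of hypothesis and investigator perceptions between arms, because one arm rates the people who applied the cream after a fresh hint that it may have been inert. The second is any later attempt to show that deceptive-arm subjects believed what they were told. That belief is what distinguishes the comparator from the open-label arm, so readers of a non-inferiority result are likely to ask for such evidence.

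**Working it through.** **Step 1: is the order stated or inferred?** It is stated. Section 2.11 puts the knowledge form first and links the perception form to it by a word of sequence; debriefing follows. Two other places need checking.

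- Section 2.8 mentions a debriefing and two questionnaires at the close without ordering them. If debriefing came first, the contamination would be greater, so this wording does not help.
- Section 4.1 says that only the educated arm repeats the knowledge test at the end, and does not say when the deceptive arm takes it. The same section later explains that completing the form before the CPT of interest is peculiar to the educated arm, and section 2.3 places the form after the study for all subjects. So the deceptive arm's first exposure is after the CPTs, as in section 2.11.

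**Step 2: does anything described earlier tell the deceptive arm that the topic is placebo?** The advertisement, the video and the spoken message (sections 2.4 and 2.10) do not. The knowledge form is thus the first described cue. The information given before consent is not available.

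**Step 3: what else could show whether the deception held?**

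| Instrument | When | What it can show |
|---|---|---|
| Expectancy questionnaire (2.3, 2.10) | Before the placebo CPT | Expected benefit; not a treatment guess |
| Deceptive placebo versus no treatment (2.13, 4.2) | From the VAS scores | Whether the comparator had an effect, not why |
| Perceived hypothesis and investigators (2.3, 2.11) | After the knowledge form | What subjects thought the study was about, after the cue |

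The first two are free of the cue but indirect. The third is the only post-CPT instrument described that could address belief directly.

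**Step 4: what is untouched?** Under section 2.8 the VAS is completed as soon as the hand leaves the water. Every pain score therefore precedes both closing forms.

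**Step 5: how many subjects are affected?** Section 2.12 gives a 10 mm margin, an SD of 21.9 mm, alpha 0.05 and 80% power. With one-sided alpha: n = 2 × (1.645 + 0.842)² × 21.9² / 10² ≈ 59.3, so 60 per group, as stated. Adding 5% gives 60 × 1.05 = 63 per group and 126 in total. All 63 deceptive-arm subjects would meet the cue. The order of the forms does not enter this calculation.

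**Step 6: what can the item estimate?** Let *s* be the share of deceptive-arm subjects who suspected placebo during the CPT, and *c* the share of the others who name it only because of the knowledge form. Suppose that all who suspected say so. The share naming placebo is then

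p = s + (1 − s) × c, so s = (p − c) / (1 − c).

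The plan provides no way to learn *c*. Purely as an assumption, take *c* between 10% and 80%.

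- If nobody suspected (s = 0), between 0.10 × 63 ≈ 6 and 0.80 × 63 ≈ 50 subjects would still name placebo.
- If 80% name placebo, then *s* is (0.80 − 0.10) / 0.90 ≈ 78% when c = 10%, and 0% when c = 80%.
- The upward bias is (1 − s) × c, which never exceeds *c*. With c = 10% it is at most 10 percentage points.

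The item is therefore biased by an unknown amount. How badly depends on *c*; a small carry-over would leave it usable.

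**The case against.** The strongest reply is that the protocol never calls this form a check of the deception. Section 2.3 describes it as a measure of perceptions, section 4.1 says only that these will be measured, and section 2.13 gives it no part in any blinding assessment or analysis population. It would be unfair to assign the form a purpose and then fault it for failing. This stands as a limit: the form could serve as such evidence, but it is not the designated check. The point survives without that role, because asking for the perceived hypothesis directly after revealing the topic weakens the question for any use.

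A reader might go further and infer that the order threatens the non-inferiority result, or that a failed deception would go unnoticed. The document supports neither. The pain scores are already recorded, so form order cannot weaken the comparator. The expectancy questionnaire precedes the cue. Section 4.2 also makes superiority of both placebos over no treatment a condition for a clinically relevant non-inferiority conclusion, so a comparator without effect would be exposed. That safeguard is only partial: the protocol's own premise is that a disclosed placebo can work too, so an effect in the deceptive arm does not prove that its subjects were deceived.

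It is also fair to say that the questionnaire items, the consent information, Figure 2 and the supplementary table comparing the interventions are not available. If the items ask what subjects thought during the immersion, or if consent mentioned placebo, the added cue would be smaller. The direction and size of any effect on the investigator ratings are unknown.

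**Conclusion.** The point holds as a modest, inexpensive improvement to a secondary measure. As written, section 2.11 gives the deceptive arm a new cue immediately before it is asked about the hypothesis and the investigators, and gives the educated arm nothing it did not already know. Answers from all 63 deceptive-arm subjects on the hypothesis, and possibly on the investigators, can reflect the preceding form. The between-arm comparison of these items is biased to that extent, and the form is unreliable evidence on whether the deception held. The primary endpoint, the placebo-versus-control endpoint, the sample size and the error rates are unaffected.

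The conclusion rests on the order stated in section 2.11, on equal allocation for the figure of 63, and on no earlier mention of placebo to the deceptive arm in material that is not shown. The 10% to 80% range is an illustration, and the conclusion does not depend on it.

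**What to change.** In section 2.11, reverse the two forms: after the last CPT, all subjects complete the questionnaire on the perceived hypothesis and the investigators, then the placebo-knowledge questionnaire, with debriefing after both. Report perception answers from subjects already tested in the present order separately from the rest.

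The practical cost is re-ordering two forms that, per section 2.6, are completed on tablets. No subjects or staff are added. The knowledge form moves by the time taken to complete the other one, so the retention interval of about 40 minutes is practically unchanged. The drawback is that section 3 reports approval granted and recruitment open since May 2019. A change now divides the perception measure between two orders, with fewer subjects in each, and the change has to be documented.

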### 2.2. Design

We will conduct a non-inferiority randomized, parallel with a nested crossover trial comparing educated open-label placebo to deceptive placebo. This monocentric study will be carried out by two licensed physiotherapists in a University Hospital near the campus.

Written informed consent will be obtained from subjects prior to their participation in the study. The investigation will consist of a single two-hour session. Participants will receive a 20€ participation compensation.

The subjects meeting the inclusion criteria (detailed below) will be randomized into two groups: (1) educated placebo or (2) conventional/deceptive placebo. Each will be subjected first to a calibration CPT, and then, in a randomized order, will receive the CPT under the condition of interest (either the Conventional placebo CPT (CPTp) or the Educated placebo CPT (CPTe)) and a Control CPT (CPTc). This is represented in Figure 1.

Regarding blinding, investigators will not be blind as they deliver the treatment openly in the educated group. Patients in the deceptive placebo group will be blinded. However, patients in the educated placebo group will not be due to the nature of OLP. The analysis will be done blindly as the analyst will not know which group received which treatment.

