## 3. Results

This research protocol has been approved by the Ethical Committee (Comité de Protection des Personnes Sud Ouest et Outre mer III) on the 28th of February 2018 under the identification 2017-A01643-50 and registered on ClinicalTrials.gov under the identification number NCT03934138. Funding has been acquired through the APICIL Foundation to conduct the investigation and compensate patients. Recruitment has started during May 2019 and will take place until the required number of subjects is recruited.

Pre-testing was conducted in order to assess logistical needs and train the investigators. Slight modifications were adopted such as the reduction of intervals between each VAS during the calibration CPT from 10 to 5 s. The instructions for the CPT were also made more precise to include instructions in regard to not touching the bottom of the tank or moving the hand during the procedure. During these pre-tests, we were able to better estimate the time needed for set-up during which the cooling of the CPT is time-consuming. The average time for inclusion is closer to one hour and a half compared to the initial two hours announced to the subjects. However, this extra time allows for a technical margin.

The final set-up is illustrated in Figure 3. Monitoring was conducted through the computer to the left. Patients had to their right the CPT tank as well as the warm water if needed. Investigators were wearing lab coats over casual clothing.

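### Debriefing on a single campus during rolling recruitment, with no listed criterion on prior knowledge, puts the deceptive arm at risk of contamination that would favour non-inferiority

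*Protocol article*

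**What the plan says.** All references are to the Protocol article.

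- **Pool (2.4).** "Participants are to be recruited via advertisements for a study of a painkiller cream, on the Grenoble University campus".
- **Period (3. Results).** "Recruitment has started during May 2019 and will take place until the required number of subjects is recruited".
- **Session (2.2).** "The investigation will consist of a single two-hour session".
- **Debriefing (2.11).** Once the subject has finished, the main investigator debriefs him or her "in order to explain the research protocol and the deception if one has taken place".
- **Eligibility (2.4).** The list opens with "Non-inclusion criteria were the following: legal impossibility to participate to the protocol" and goes on to conditions affecting the stimulus, allergy to the cream and pain medication. Prior knowledge of the study is not on it.
- **Belief measures.** After the three cold pressor tests and before debriefing, "Subjects then fill out a questionnaire on their perception of the research hypothesis as well as their perception of the investigators" (2.11). Also, "Before the CPT treatment, an expectancy questionnaire will be used" (2.3).
- **Blinding (2.2 and 2.10).** Subjects in the deceptive arm are to be blinded. Those in the educated arm are told the cream is a placebo.
- **Analysis (2.13).** Non-inferiority is judged on a one-sided 95% confidence interval against a 10 mm margin, by intention to treat and per protocol. Neither belief measure is given a role in it.
- **Supporting condition (4.2).** A clinically relevant non-inferiority conclusion also requires both placebos to be superior to no treatment.

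**The concern.** The comparator works only if its recipients believe the cream may be active. Each debriefed subject goes back to the campus from which later subjects are drawn, and the listed criteria would admit someone who has heard that the cream is inert.

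The two arms are not equally exposed. An informed subject in the educated arm is told about the placebo anyway and still receives the planned intervention. An informed subject in the deceptive arm gets neither a working deception nor the education. Such subjects would probably report more pain under placebo, which raises the comparator's mean and moves educated minus deceptive in the favourable direction. In a non-inferiority trial that is the anti-conservative direction: the educated placebo could be declared non-inferior to a deceptive placebo that was only partly delivered.

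**Working it through.** **Inputs from section 2.12 and 2.13:** margin 10 mm; SD 21.9 mm; one-sided alpha 0.05; power 80%; 60 per group; 5% allowance for non-usable data.

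**Inputs assumed, because the documents do not give them:** the fraction f of the deceptive arm who arrive informed, and the mean effect E in mm that each of them loses.

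**Step 1, the plan's own figure.** n = 2 × (1.645 + 0.842)² × 21.9² / 10² = 59.3, rounded up to 60 per group. Then 120 × 1.05 = 126. Both stated figures reproduce.

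**Step 2, standard error.** SE = 21.9 × √(2/60) = 4.00 mm.

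**Step 3, effect of leakage.** Let the true difference under full concealment equal the margin, so that the correct pass rate is 5%. If informed deceptive-arm subjects respond like the educated arm, each loses E = 10 mm and the expected difference falls to 10(1 − f). Non-inferiority is declared when estimate + 1.645 × SE < 10, so

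P(false non-inferiority) = Φ(10f / 4.00 − 1.645).

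| f | Bias (mm) | Argument of Φ | Probability |
|---|---|---|---|
| 0 | 0 | −1.645 | 5.0% |
| 10% | 1.0 | −1.395 | 8.2% |
| 20% | 2.0 | −1.145 | 12.6% |
| 30% | 3.0 | −0.895 | 18.6% |

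**Step 4, sensitivity.**
- At f = 5% the result is 6.4% for E = 10 mm and 8.2% for E = 20 mm.
- With E = 20 mm, so that informed subjects do worse than the educated arm, f = 10%, 20% and 30% give 12.6%, 26.0% and 44.3%.
- The primary regression adjusts for pain in the control test. With an assumed correlation of 0.5 the SE shrinks to 4.00 × √0.75 = 3.46 mm. With E = 10 mm the three probabilities then become 8.8%, 14.3% and 21.8%. A more precise analysis makes the same bias more costly.

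**Step 5, would superiority over no treatment catch it?** Assume effects of 20 mm (deceptive) and 10 mm (educated) and a within-subject correlation of 0.5. The paired SE is 21.9 × √(2 × 0.5/60) = 2.83 mm. With 20% of the deceptive arm informed and responding like the educated arm, its mean effect is 0.8 × 20 + 0.2 × 10 = 18 mm, or 18/2.83 = 6.4 SE. The condition is met easily although the comparator is diluted.

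**The case against.** The strongest reply is that this rests on silence in a condensed article. Debriefing and screening scripts, and sensitivity analyses, are usually left to the full protocol or analysis plan, which are not shown. That stands for the confidentiality request: its absence here does not show that none is made. It has less force for eligibility, because section 2.4 sets out the criteria and prior knowledge is not among them.

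Several stronger readings are tempting but not supported:

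- **That every subject is told of the deception.** Section 2.11 says the deception is explained where one occurred. All subjects have the research protocol explained, which would probably reveal it, but that is an inference.
- **That the deceptive arm is being contaminated.** Nothing reports leakage, campus size or contact between participants, and early recruits could have met few debriefed subjects or none.
- **That nothing checks what subjects believed.** The perceived-hypothesis questionnaire precedes debriefing and could reveal suspicion. The gap is that no described analysis uses it and that, as described, it does not separate knowledge held on arrival from a guess formed during the session.
- **That both analysis sets must share the error.** Section 2.13 does not list what counts as a deviation. A subject known to be unblinded might be classed as one, but as written the per-protocol set does not ensure it.
- **That the registry entry discloses the design.** Only its number is in the documents.

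The superiority condition in section 4.2 is a real safeguard against a comparator that has lost its effect altogether. Step 5 shows that it does not protect against partial dilution.

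**Conclusion.** The point holds as a risk. Rolling recruitment on one campus, debriefing at the end of each single session, and criteria that admit informed volunteers together expose the only arm that depends on concealment, and the likely bias is toward non-inferiority. Its size cannot be derived from the documents. Under the Step 3 assumptions the nominal 5% error becomes about 8%, 13% and 19% at informed fractions of 10%, 20% and 30%. With few informed subjects the effect is modest. The point still deserves action, because whether a subject knew on arrival cannot be reliably recovered at analysis and asking at entry costs little.

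**What to change.** 1. **At entry.** At the eligibility check that section 2.9 already places before consent and before the envelope is opened, ask neutrally whether the volunteer has heard anything about the study beyond the advertisement. Do not include those who know its content, and add this to the criteria in section 2.4. Applied before randomization, the rule affects both arms alike.
2. **At debriefing.** If this is not already done, ask each subject not to share the content until recruitment closes. The debriefing stays where it is.
3. **For subjects already enrolled.** State how the planned perceived-hypothesis questionnaire will be used in a sensitivity analysis of the primary endpoint, with the same prior-knowledge rule in both arms. Removing informed subjects from the deceptive arm only would break the randomized comparison. Because the questionnaire is completed after treatment and cannot cleanly date the knowledge, this analysis is supportive only.

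**Cost.** A few volunteers are screened out and a small amendment is needed during recruitment. There is a slight chance that the question itself prompts suspicion, which neutral wording limits.
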